## Abstract

**Background:**

Social anxiety is increasingly prevalent among youths, leading to social withdrawal, isolation, and heightened depression risk. Mobile health (mHealth) interventions offer anonymity, accessibility, and personalized support, but their effectiveness and cost-effectiveness for young individuals with social anxiety remain unclear.

**Objective:**

This randomized controlled trial aims to evaluate the effectiveness and cost-effectiveness of a mobile-based psychoeducation program (OkeyMind) for mitigating social anxiety symptoms among youth.

**Methods:**

Participants aged 15 years through 24 years with mild or more severe social phobia (Social Phobia Inventory [SPIN] ≥25) and access to WeChat will be recruited and screened onsite and then randomly assigned to the intervention or waiting list control group. The study will recruit 180 participants, with 90 in each group. The intervention group will receive a 1-month mobile psychoeducation program (OkeyMind), which includes both psychoeducation and meditation components, with all content fully automated. The waiting list control group will receive the same intervention after 3 months. The primary outcome is social anxiety symptoms measured using SPIN. Secondary outcomes include depression (Patient Health Questionnaire-9) and health-related quality of life (EuroQol-5). Assessments will be conducted at baseline, postintervention, and a 3-month follow-up.

**Results:**

Recruitment began in September 2024. The study was funded in April 2024, and the first participant was enrolled in September 2024; as of the end of March 2025, 132 participants had been recruited. Recruitment is ongoing. Data collection will conclude in July 2025, after which data analysis will begin and be completed in August 2025, with primary findings targeted for publication in spring 2026.

**Conclusions:**

This research evaluates the effectiveness and cost-effectiveness of OkeyMind, a mobile-based psychoeducation program, for reducing social anxiety symptoms among youth. OkeyMind might be a promising strategy for combating social anxiety, especially in low- and middle-income countries with limited medical resources. If effective, this intervention could provide an accessible, cost-effective approach to managing social anxiety, particularly in resource-limited settings.

**Trial Registration:**

ClinicalTrials.gov NCT06490315; https://clinicaltrials.gov/study/NCT06490315

**International Registered Report Identifier (IRRID):**

PRR1-10.2196/64518

## Introduction

### Social Anxiety Among Youths

Social anxiety, also known as social phobia, is characterized by a marked fear of social situations where individuals may be scrutinized by others, often leading to avoidance behaviors and distress [1,2]. A core component of social anxiety is heightened sensitivity to negative evaluation, reinforcing self-doubt and anticipatory anxiety [1]. This persistent self-doubt and anticipatory anxiety can lead to social withdrawal, reducing social support and reinforcing feelings of isolation. Over time, these factors contribute to a negative self-concept and sense of helplessness, both of which are strongly associated with depression [3]. Numerous studies have demonstrated the link between social anxiety and depression [3-5]. A study tracking 2548 participants aged 14 years through 24 years from diverse communities found that social anxiety frequently coexists with major depression and, in most cases, social anxiety develops first, preceding the onset of depression [6].

Moreover, a frequently overlooked aspect in academic discussions is the distinction in depression between youths and the general adult population. This difference is significant due to various factors. First, youths experience rapid physical, emotional, and cognitive development, making them more vulnerable to depression during this period of intense change [7]. Additionally, young individuals are still developing effective coping strategies, making them more susceptible to negative influences, whereas adults, with more life experience, generally have better-established coping mechanisms [8]. Furthermore, youths often depend on guardians for access to mental health care, which can be hindered by stigma or a lack of awareness, while adults have more autonomy in seeking professional help [9]. Therefore, there is a growing demand for interventions specifically designed to address social anxiety in youths, tailored to the distinct characteristics unique to this age group.

### mHealth Interventions as an Effective and Cost-Effective Method

Over the last decade, there has been a notable increase in the use of mobile health (mHealth) technologies to improve both access to and engagement with treatments for social anxiety [10]. Accumulated clinical evidence broadly supports this widespread promotion, especially in the young population. mHealth solutions in the delivery of interventions are widely accepted by youth users. Most young adults own a smartphone, have accessed mHealth apps, and report a stated preference for engaging with health services in this manner [11]. Moreover, mHealth interventions are capable of replicating, and even surpassing, the therapeutic gains achieved through traditional face-to-face treatments [12]. Studies indicate that these approaches are producing promising positive effects in reducing psychological distress, including symptoms of social anxiety [13-15]. The mobile intervention being evaluated in this study, OkeyMind, is designed to meet the specific needs of the target population and intended outcomes by leveraging WeChat’s extensive global user base of 1.382 billion active users [16]. It provides a highly accessible and lightweight alternative to traditional mobile apps by eliminating the need for additional downloads and storage. Additionally, OkeyMind incorporates innovative features, including personalized feedback mechanisms for tracking progress and adaptive algorithms that tailor the intervention to individual needs. Given that young users tend to place a high value on privacy, convenience, and customization, this approach ensures greater usability and relevance for the target population [17,18].

Moreover, the delivery of mHealth services has demonstrated significant cost efficiency, a conclusion strongly supported by recent meta-analyses and synthesis studies [19,20]. This is especially evident in the realm of mental health, where mHealth solutions stand out for their ability to eliminate the need for physical infrastructure [21]. OkeyMind, a WeChat miniprogram, has a lower development complexity and shorter implementation cycle than a standalone mobile app, as it operates within the WeChat ecosystem, eliminating the need for separate app store approvals and extensive backend infrastructure [22,23]. Therefore, OkeyMind has the potential to be more easily accessible to a wider audience, including individuals who may face barriers to traditional in-person therapy, such as geographical limitations, scheduling conflicts, or stigma associated with seeking help [24].

### Research Gaps

Despite the rising prevalence of social anxiety among youths, there is limited high-quality empirical evidence, particularly from randomized controlled trials, on effective interventions tailored to youth with social anxiety symptoms. mHealth interventions have shown promise, yet their efficacy remains underexplored [25]. Additionally, the scarcity of economic evaluations for psychological interventions becomes especially critical during global economic downturns, when funding for mental health support and research typically decreases [26]. The absence of economic evaluations further complicates the situation by not providing essential data on the interventions’ cost-effectiveness and benefits. Without this information, policymakers struggle to allocate limited resources effectively, risking the sustainability of mental health services and potentially increasing the unmet need for psychological support in populations affected by economic hardship [27].

### Research Objectives and Hypotheses

The primary objective is to assess the effectiveness of the OkeyMind mobile-based psychoeducation program on mitigating social anxiety symptoms among young adults aged 15 years through 24 years. The secondary objective is to evaluate the cost-effectiveness of the OkeyMind program as a mental health intervention tool, aiming to ascertain whether the financial investment in OkeyMind translates into significant economic and health-related advantages. The study tests 2 hypotheses: (1) OkeyMind is more effective than the control condition in reducing social anxiety symptoms among youths, and (2) OkeyMind is more cost-effective than the control condition for this population.

## Methods

### Trial Design

The design is a 2-arm, single-blind, parallel-group, randomized controlled trial to test whether the mHealth intervention program (OkeyMind), compared with the waiting list control, leads to reductions in social anxiety symptoms among youths. No additional interventions are provided beyond the OkeyMind program during the research period. Assessments will be carried out at baseline (T0), posttreatment (T1), and follow-up (T2). The choice of a 3-month follow-up assessment is primarily driven by its established feasibility in similar studies [24]. The protocol has been registered with ClinicalTrials.gov (NCT06490315). Figure 1 shows the CONSORT (Consolidated Standards of Reporting Trials) flow diagram.

**Figure 1 figure1:**
[figure not shown]
CONSORT (Consolidated Standards of Reporting Trials) flow diagram.

### Ethical Considerations

The protocol and informed consent form received approval from the Hong Kong Shue Yan University of the Human Research Ethics Committee (HREC 24-06(6)). Eligible adult participants who are willing to join the study will provide consent by signing an online consent form. Eligible adolescent participants will be required to obtain parental consent before enrollment. To reduce the likelihood or detection of harm, various safety and security procedures will be implemented, such as excluding potentially psychologically ill participants during the screening stage.

To ensure the confidentiality and security of participant data, all collected information is securely encrypted during transmission and storage, preventing unauthorized access. Access to participant data is strictly limited to authorized research personnel. Additionally, personally identifiable information is anonymized or de-identified wherever possible to safeguard participant privacy. Each eligible participant will receive compensation of approximately HK$ 190 (US $25) for their participation in the study.

### Randomization and Blinding

Participants will be randomized after the baseline assessment using computer-generated block randomization with a 1:1 allocation ratio within pre-established blocks of 90 participants. To ensure balance, a randomized blocking schema with block sizes of 2, 4, or 6 will be implemented. An independent research assistant, uninvolved in statistical analysis, will conduct the randomization. To minimize bias, participants will remain blinded to their group assignment.

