### Recruitment

The study will be conducted in school settings, including middle schools and tertiary institutions, across China. The trial aims to enroll 180 participants, with 90 assigned to each group [28]. This sample size accounts for an anticipated attrition rate of 10% and is expected to offer 90% statistical power. This determination is based on using an independent group *t* test, a significance level of .05, and an effect size of 0.35 (Cohen *d*), which falls within the small-to-medium range [29]. To recruit enough participants, school faculty help with recruitment, and digital flyers and promotional videos are shared through WeChat and school online platforms.

The participant inclusion criteria include (1) youths aged between 15 years and 24 years old who are (2) exhibiting mild or more severe social phobia (ie, Social Phobia Inventory [SPIN] score ≥25) and (3) have a smartphone with WeChat installed and basic internet literacy. The exclusion criteria include (1) being unable to attempt a baseline assessment (eg, due to being unpermitted to leave a psychiatric ward), (2) currently receiving another intensive psychological intervention, (3) currently holding an active suicidal plan, and (4) having a current diagnosis of psychological disorders (eg, schizophrenia, bipolar disorder). These data will be collected through self-report questionnaires, including questions such as: “Have you been previously diagnosed with any psychological disorders (eg, schizophrenia, bipolar disorder)? If yes, please specify.” Additionally, university tutors, who are familiar with students’ mental health conditions, will assist with identifying ineligible participants. Participants will be recruited and screened offline but will complete all interventions and assessments online. Participants are briefed through online tutorial video clips in the OkeyMind miniprogram; these clips demonstrate the research flow regarding intervention timing, follow-up frequency, and usage intensity.

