#### Control Group—Waiting List

Participants in the waiting list control group will have access to the OkeyMind intervention withheld until after the 3-month follow-up assessment. To prevent confounding effects from relevant concomitant care and interventions, participants will be required to refrain from receiving any other treatments or interventions specifically targeting social phobia during the study period.

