### Outcomes

Basic demographic and clinical data, including age, gender, region, and socioeconomic status, will be collected. The primary outcome will be social anxiety symptoms, assessed using SPIN. Secondary outcomes include depressive symptoms, measured using the Patient Health Questionnaire-9 (PHQ-9), and quality of life, evaluated using the EQ-5D-5L, which will also be used for cost analysis. All outcomes will be self-assessed using online measurements at baseline, postintervention, and the 3-month follow-up (Figure 2).

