### Limitations

Given that all intervention sessions and evaluations are conducted online and the research period extended over several months, there is potential for a relatively high attrition rate compared with on-site interventions. To address this issue, several measures are implemented. First, during the screening stage, interviews are scheduled to ensure each participant has the proper motivation and desire to participate, helping to select committed individuals more likely to complete the program. Second, support is provided during interventions and assessments, with manpower allocated to address any issues. Reminder systems, such as texts or calls, are implemented to prompt participants when delays occur, aiming to keep them engaged and on track. Third, the technology and software team continuously improves the user experience based on participant feedback, enhancing video quality and reducing buffering times to ensure a smoother and more enjoyable experience, thus reducing dropout rates due to technical frustrations.

Additionally, the technological nature of OkeyMind may limit the program’s generalizability. Youths familiar with using social media and WeChat miniprograms are likely to benefit more from the intervention than older adults who may be less familiar and comfortable with these digital platforms. This discrepancy in technological proficiency could impact the overall effectiveness and reach of the program across different age groups, potentially introducing bias in the results and affecting the external validity of the study. Future research should consider addressing this limitation by exploring ways to make the program more accessible and user-friendly for older adults.

Last, achieving complete participant blinding could be challenging, particularly in behavioral interventions such as this study. Participants could infer their group assignment, introducing potential performance and self-report biases. However, using a waiting list rather than a no-treatment control ensured that control participants still anticipated full access to the intervention after follow-up, potentially softening, though not eliminating, these biases. Future studies should adopt more rigorous designs, such as concurrently running 2 active intervention arms, to mitigate performance and self-report biases.

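### The Methods claim that participants are blinded, which a waiting-list design with self-rated outcomes cannot deliver and which the article's own Limitations contradict

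*Protocol article*

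**What the plan says.** Trial Design describes a "2-arm, single-blind, parallel-group, randomized controlled trial". Randomization and Blinding says who is blinded: "To minimize bias, participants will remain blinded to their group assignment". That sentence carries no qualification.

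Other sections describe a different situation:

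- Control Group—Waiting List: "Participants in the waiting list control group will have access to the OkeyMind intervention withheld until after the 3-month follow-up assessment".
- Recruitment, on the tutorial videos used to brief participants: "these clips demonstrate the research flow regarding intervention timing, follow-up frequency, and usage intensity".
- Outcomes: "All outcomes will be self-assessed using online measurements". The instruments are SPIN (primary), PHQ-9 and EQ-5D-5L (secondary).
- Limitations: complete blinding of participants may prove difficult, they may deduce their arm, and this could bias both behaviour and self-report. As mitigation it says that "control participants still anticipated full access to the intervention after follow-up", which may lessen these biases without removing them.

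**The concern.** A blinding statement tells the reader which biases the design has dealt with. Participant blinding matters most when participants are also the outcome assessors, as they are here. If the label is wrong, a reader who takes the design from the Methods will credit the SPIN comparison with a protection it does not have. An arm difference on SPIN would then be read as an effect of the programme's content, when it could also contain the effect of knowing that one is being treated or is waiting. The same holds for PHQ-9 and for EQ-5D-5L, and through the latter for the QALYs in the cost-effectiveness analysis.

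**Working it through.** The plan gives no figure on this point, so the check is a comparison of sections.

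1. **Who is said to be blinded?** Only participants. The research assistant who randomizes is described as independent and not involved in the analysis, which is a statement about separation of tasks and not about masking. As the article is written, the single-blind label rests on participants alone.

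2. **Can participants be unaware of their arm?** One arm works through a 1-month programme of videos and meditation, with reminders to keep to it. The other has no access until after the 3-month assessment. The article describes no sham or active comparator that could make the two experiences alike. From the start of the intervention period, a participant can therefore tell which condition applies. This is an inference from the design, and it does not depend on anyone announcing the allocation.

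3. **What do participants know in addition?** The briefing videos cover when the intervention takes place. The article does not say whether the two arms see the same videos, so this supports step 2 without settling it. The Limitations section is stronger evidence. Its argument that the expectation of later access softens bias works only if controls know that their access comes later, so the mitigation presupposes the loss of blinding.

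4. **Who measures the outcome?** The participant, for all three instruments at all three assessments. Automatic data capture by the miniprogram (Effectiveness Analyses) removes manual entry of the data, but it does not change who gives the answers.

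5. **Do the sections agree?** No. Trial Design and Randomization and Blinding state blinding as a fact. The Control Group section describes a comparison in which it cannot be maintained. Limitations treats its failure as a possibility. These statements cannot all stand as the description of one trial.

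**The case against.** The strongest reply is that the article discloses the problem. Limitations names the mechanism (participants working out their arm) and the resulting biases, says the waiting list does not eliminate them, and recommends two active arms for future studies. Anyone who reads the whole article meets the waiting list, the self-rated outcomes and the caveat. This stands in part: a reader might infer that the risk has been hidden, and the text does not support that. But the caveat treats as possible what this design makes the expected state, and it leaves the two Methods statements uncorrected.

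A second reply is that the consent pages and the flow diagram are not shown, so what controls were told cannot be established. That also stands. A reader might infer from the Limitations that controls were expressly told their allocation. The text says only that they anticipated later access. The point does not need the stronger statement. Even someone kept unaware that another arm exists still knows whether the programme is in use.

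A third reply is that single-blind might refer to the analysts. The article attaches blinding to participants and to no one else. Its silence on analysts is not a fault, because that detail may sit in the full protocol or the analysis plan.

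**Conclusion.** The point holds as an internal contradiction: the Methods claim participant blinding, and the comparator and outcome assessment described in the same article rule it out. The conclusion rests on one inference, that participants recognise their arm from having or lacking the programme. The article itself goes only as far as calling complete blinding difficult.

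Its reach is every self-rated outcome and the QALYs. Its size in SPIN points or standard deviations is unknown. A reader might infer that a stated share of the planned effect (Cohen d of 0.35) could be reporting bias. Any such share would come from an assumed bias, since the documents give neither its amount nor its direction, so none is claimed here.

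The contradiction does not invalidate the randomized comparison. It changes what may be concluded from it.

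**What to change.** In Trial Design and in Randomization and Blinding, replace the single-blind label and the sentence on participant blinding with a statement that the trial is open-label for participants and that outcomes are self-reported. Bring Limitations into line, so that it describes lack of blinding as a feature of the design and no longer as a possibility.

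Word the conclusion of the report as an effect on self-reported symptoms compared with an unblinded waiting list, which may include expectancy and reporting effects. Apply the same wording to PHQ-9, EQ-5D-5L and the cost-effectiveness result.

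Optionally, run the primary model on masked arm codes and reveal the arms only once the model output is final. This is feasible because analysis is planned to start after data collection ends in July 2025. It guards against bias from the analysts only and does nothing about self-report bias.

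The cost is a few sentences, a coded arm variable if the option is taken, and a less favourable design label. Recruitment, sample size, intervention and assessments are unaffected.

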### Recruitment

The study will be conducted in school settings, including middle schools and tertiary institutions, across China. The trial aims to enroll 180 participants, with 90 assigned to each group [28]. This sample size accounts for an anticipated attrition rate of 10% and is expected to offer 90% statistical power. This determination is based on using an independent group *t* test, a significance level of .05, and an effect size of 0.35 (Cohen *d*), which falls within the small-to-medium range [29]. To recruit enough participants, school faculty help with recruitment, and digital flyers and promotional videos are shared through WeChat and school online platforms.

The participant inclusion criteria include (1) youths aged between 15 years and 24 years old who are (2) exhibiting mild or more severe social phobia (ie, Social Phobia Inventory [SPIN] score ≥25) and (3) have a smartphone with WeChat installed and basic internet literacy. The exclusion criteria include (1) being unable to attempt a baseline assessment (eg, due to being unpermitted to leave a psychiatric ward), (2) currently receiving another intensive psychological intervention, (3) currently holding an active suicidal plan, and (4) having a current diagnosis of psychological disorders (eg, schizophrenia, bipolar disorder). These data will be collected through self-report questionnaires, including questions such as: “Have you been previously diagnosed with any psychological disorders (eg, schizophrenia, bipolar disorder)? If yes, please specify.” Additionally, university tutors, who are familiar with students’ mental health conditions, will assist with identifying ineligible participants. Participants will be recruited and screened offline but will complete all interventions and assessments online. Participants are briefed through online tutorial video clips in the OkeyMind miniprogram; these clips demonstrate the research flow regarding intervention timing, follow-up frequency, and usage intensity.

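### The stated 90% power does not follow from its own inputs: 90 per arm, 10% attrition, a t test at .05 and d = 0.35 give about 60%

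*Protocol article*

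**What the plan says.** The Recruitment section of the protocol article sets the size: "The trial aims to enroll 180 participants, with 90 assigned to each group". It then states: "This sample size accounts for an anticipated attrition rate of 10% and is expected to offer 90% statistical power". The method follows: "This determination is based on using an independent group *t* test", with "a significance level of .05, and an effect size of 0.35" on the Cohen d scale. Randomization and Blinding confirms equal allocation: "computer-generated block randomization with a 1:1 allocation ratio". The article does not say whether the test is one- or two-sided. The power statement uses no baseline correlation and no gain from repeated measurement.

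The Effectiveness Analyses section plans a different analysis for the primary outcome. It is a linear mixed-effects model of the post-intervention and 3-month responses, with baseline, group and a time-by-group interaction as fixed effects and a random intercept per participant.

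**The concern.** Every input needed to check the power is printed beside it, apart from sidedness. A standardised difference of 0.35 is modest, and 81 analysed per arm is small for 90% power to detect it with an unadjusted two-sample comparison. If the printed figure is wrong, the justification for the sample size is wrong as published. Anyone who weighs the primary result against a claimed 90% power would then credit the stated design with more sensitivity than it has.

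**Working it through.** **Inputs.** From Recruitment: 90 enrolled per arm, 10% attrition, alpha .05, d = 0.35, independent-groups t test. From Randomization and Blinding: 1:1 allocation. Analysed per arm: 90 × 0.9 = 81. Sidedness is not given, so both were tried.

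**Attempt to reproduce 90%.** For two equal groups the noncentrality parameter is d × √(n/2), with 2n − 2 degrees of freedom. Power comes from the noncentral t distribution.

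- n = 81: 0.35 × √40.5 = 2.227
- n = 90: 0.35 × √45 = 2.348

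| Analysed per arm | Two-sided .05 | One-sided .05 |
|---|---|---|
| 81 (10% attrition) | 60.0% | 71.7% |
| 90 (no attrition) | 64.6% | 75.6% |

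The normal approximation gives nearly the same values (60.5%, 65.1%, 72.0% and 75.9%), so the choice of formula does not matter. The best case is still about 14 points short of 90%.

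**Size that the stated inputs need for 90%.** The normal formula is n = 2 × (1.960 + 1.282)² / 0.35² ≈ 172 per arm. The exact t calculation gives 172.5, so 173 analysed per arm. Allowing for attrition, 173 / 0.9 = 192.2, so 193 enrolled per arm or 386 in total. A one-sided test still needs 141 analysed per arm (140.5 rounded up).

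**What 81 per arm can detect (two-sided .05 t test).** d = 0.51 at 90% power and d = 0.44 at 80%.

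**Possible gain from the planned model.** The correlations here are assumptions. For one post-baseline time point, adjusting for a baseline with correlation r to the outcome scales the effect to d / √(1 − r²). With 81 per arm, two-sided:

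| Assumed r | Effective d | Power |
|---|---|---|
| 0.5 | 0.35 / 0.866 = 0.404 | 72% |
| 0.6 | 0.35 / 0.800 = 0.438 | 79% |
| 0.7 | 0.35 / 0.714 = 0.490 | 87% |
| 0.73 | 0.35 / 0.683 = 0.512 | 90% |

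If the treatment effect were averaged over both visits, the residual variance would be (1 + ρ)/2 − r², where ρ is the correlation between the two visits. Assume d = 0.35 at each visit and ρ of 0.6 to 0.7. Then r = 0.5 gives a variance of 0.55 to 0.60 and power of about 82–85%. With r = 0.6 the variance is 0.44 to 0.49 and power is about 89–92%.

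**The case against.** The strongest objection is that the trial will not be analysed with a t test. The planned mixed model adjusts for baseline and uses two post-baseline assessments, and under plausible correlations its power could come near or reach 90%. This stands as a limit on the consequence. It does not rescue the statement, because the article attributes its 90% to the t test and supplies no correlation from which another figure could be derived. Nor is this a detail left to a fuller document, since the figure contradicts the inputs printed with it.

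Three stronger readings are tempting, and the article does not support them.

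- **That the trial will miss a true effect of 0.35 about 4 times in 10.** That rate (100% − 60%) belongs to the stated t test only. On the single-visit assumptions above, the adjusted model would miss it roughly 1 to 3 times in 10.
- **That the 10% attrition contradicts the Limitations section.** That section says "there is potential for a relatively high attrition rate compared with on-site interventions". This is a relative statement about a possibility, with no number, and it is followed by three measures to contain dropout. An assumption of 10% is compatible with it.
- **That enrolling only people with SPIN of 25 or more pushes adjusted power down to a particular range.** That would depend on the share of scores above the cutoff and on whether d is standardised to the selected or the unselected population. The article gives neither. The SPIN test-retest value of 0.73 that it reports is also not stated to be a 1- or 3-month baseline-outcome correlation in this sample.

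**Conclusion.** The power statement is wrong as written. On the stated inputs, power is 60% two-sided with 81 analysed per arm, 30 points below the printed 90%, and no reading of those inputs exceeds 76%. For two-sided 90% power the enrolled sample would have to be a little more than twice as large (193 against 90 per arm). This conclusion rests only on the article's own figures; the one open choice, sidedness, was tried both ways. The power of the mixed model that will actually be used cannot be established from the article. The figures shown for it are illustrations under assumed correlations.

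**What to change.** Keep 180 participants and correct the paragraph in Recruitment in one of two ways.

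1. Restate the t-test figure, for example: *With 90 per arm and 10% attrition (81 analysed), a two-sided .05 t test has 60% power for d = 0.35; the detectable effect is d = 0.51 at 90% power and d = 0.44 at 80%.*
2. Base the power on the planned baseline-adjusted mixed model. State the time point or the average over visits to which it refers, the assumed baseline-outcome correlation and (if visits are averaged) the between-visit correlation, and show power over a range of them. The single-visit values above, 72% at r = 0.5 to 90% at r = 0.73, show how strongly the answer depends on that assumption.

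Either version should say whether the test is one- or two-sided. The cost is one rewritten paragraph, carried into the trial report, and a less favourable stated power. No further participants are needed.
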